# Impact on mortality of the timing of renal replacement therapy in patients with severe acute kidney injury in septic shock: the IDEAL-ICU study (initiation of dialysis early versus delayed in the intensive care unit): study protocol for a randomized controlled trial

**DOI:** 10.1186/1745-6215-15-270

**Published:** 2014-07-07

**Keywords:** severe acute kidney injury, septic shock, renal replacement therapy, intensive care

## Abstract

**Background:**

One of the most dreaded complications of septic shock is acute kidney injury. It occurs in around 50% of patients, with a mortality rate of about 60% at 3 months. There is no consensus on the optimal time to initiate renal replacement therapy. Retrospective and observational studies suggest that early implementation of renal replacement therapy could improve the prognosis for these patients.

**Methods/design:**

This protocol summarizes the rationale and design of a randomized, controlled, multicenter trial investigating the effect of early versus delayed renal replacement therapy in patients with severe acute kidney injury in early septic shock. In total, 864 critically ill adults with septic shock and evidence of acute kidney injury, defined as the failure stage of the RIFLE classification, will be enrolled. The primary outcome is mortality at 90 days. Secondary outcomes include safety, number of days free of mechanical ventilation, number of days free of renal replacement therapy, intensive care length of stay, in-hospital length of stay, quality of life as evaluated by the EQ-5D and renal replacement therapy dependence at hospital discharge. The primary analysis will be intention to treat. Recruitment started in March 2012 and will be completed by March 2015.

**Discussion:**

This protocol for a randomized controlled study investigating the impact of the timing of renal replacement therapy initiation should provide an answer to a key question for the management of patients with acute kidney injury in the context of septic shock, for whom the mortality rate remains close to 60% despite improved understanding of physiopathology and recent therapeutic advances.

**Trial registration:**

ClinicalTrials.gov identifier NCT01682590, registered on 10 September 2012.

## Background

The incidence of acute kidney injury (AKI) in patients with septic shock is around 50% [1-3]. In severe septic shock, the need for renal replacement therapy (RRT) contributes to increasing the risk of death from less than 40% in septic shock without AKI, to over 60% in the forms associated with severe AKI requiring RRT [4]. It is now proven that AKI associated with sepsis is an independent risk factor for mortality [5,6], not just an epiphenomenon related to the severity of the patients’ illness. The discrimination of septic and non-septic AKI may have clinical relevance for clinicians [7]. Some experimental studies suggested that septic AKI may be characterized by a distinct pathophysiology [8]. Thus, septic AKI may have differences in clinical outcomes and responses to interventions compared to non-septic AKI.

### Initiation of renal replacement therapy: state of the art

In chronic renal failure patients, there is no benefit to initiating dialysis until the glomerular filtration rate drops to less than 7 mL/min (except in case of uremic syndrome). This is usually the beginning of dependence on dialysis for these patients [9]. The situation is different for patients with AKI, and the optimal time to start RRT remains unknown. In current practice, the initiation of RRT is sometimes very early (i.e. within the first 24 hr) [10], but may sometimes be delayed, whereby diuresis is stimulated with diuretics, and RRT is started only with the appearance of serious events, rather than following a proactive decision based on the severity of renal impairment [11]. Indeed, this attitude is justified by the possibility that appropriate early treatment of sepsis may limit the progression to renal failure [12].

In one historical study published in 1960, Teschan *et al*. [13] introduced the concept of prophylactic hemodialysis, advancing the hypothesis that the prevention of uremic syndrome could prevent its complications, including sepsis. In this study, the threshold for defining RRT was a urea level above 57 mmol/L, and dialysis was initiated 2 to 3 days after the diagnosis of AKI. Since this initial study, several authors have compared early versus late therapy, using different criteria and thresholds.

To the best of our knowledge, there is only one randomized controlled trial to date that has examined the benefits of early initiation of RRT in critically ill patients with AKI [14]. In this study, which compared two doses of dialysis, a secondary analysis compared early (within 12 hr of diagnosis) versus late hemofiltration (when the patient fulfilled the conventional criteria for RRT, namely a plasma urea level of >40 mmol/L, potassium of >6.5 mmol/L or severe pulmonary edema). On average, hemofiltration was started 7 hr after inclusion in the early group and a mean of 42 hr after inclusion in the late group. No significant differences were found, either in terms of mortality at 28 days, or in terms of recovery of renal function. However, the study was undersized to answer the question of the timing of RRT (analysis of 106 patients) and was not specifically designed to test this hypothesis.

Several observational and retrospective studies that have been conducted with patients with AKI, with or without sepsis, suggest on the contrary that there may be a benefit to early initiation of RRT [15-17]. A meta-analysis published in 2008 by Seabra [18], which included studies published over the last five decades, found a statistically significant reduction in mortality with early RRT in 18 cohort studies, with a relative risk of 0.72 (95% confidence interval 0.64 to 0.82, *P* < 0.001). In one prospective, multicenter, observational study [19], the timing of RRT was stratified into early and late by median urea (24.2 mmol/L) and by median creatinine (309 μmol/L) at the time RRT was started. There was no significant difference in adjusted hospital mortality when stratified by median serum urea at the time of RRT initiation. Conversely, when stratified by creatinine levels, late RRT was associated with lower mortality. Timing was also categorized temporally from ICU admission into early (<2 days), delayed (2 to 5 days) and late (>5 days), and late RRT was associated with increased mortality.

Other authors have tried to initiate very early RRT as a treatment for the initial phase of septic shock, with discordant results [20,21]. In these studies, hemofiltration techniques were introduced before the onset of established AKI, more with a view to immunomodulation than to treating the AKI itself. Interestingly, a recent retrospective multicenter observational study [22] found a U-shaped association between the timing of RRT initiation and in-hospital mortality, with reduced mortality when initiation of RRT was between 2 and 3 days after ICU admission. The peak mortality when RRT was initiated very early was related to the extreme severity of disease in these patients, whereas age and septic complications were responsible for the highest mortality in the case of late RRT (after D4).

The overall results of these studies would seem to indicate that there is a benefit from early initiation of RRT, but the exact definition of early remains to be determined, as does the definition of the criteria for AKI necessitating RRT. The question of the right time to begin RRT remains unanswered and controversial, and poses a real problem in the management of patients with septic shock and AKI. In this context, we propose a randomized, multicenter, controlled trial on the impact on mortality of the timing of RRT initiation in patients with acute kidney failure in septic shock.

### Objectives

The primary objective is to assess whether the timing of RRT initiation (early versus delayed) has an impact on mortality at 90 days in patients with AKI at the failure stage according to the RIFLE criteria [23] (see details below in Study definitions), during the initial phase of septic shock. The secondary objectives are: (1) to evaluate the impact of early versus delayed initiation of RRT on key secondary endpoints including: 28-day, 180-day and 1-year mortality; number of days free of mechanical ventilation; number of days free of RRT; ICU length of stay; hospital length of stay; and 90-day and 1-year quality of life as evaluated by the EQ-5D questionnaire; (2) to compare the efficacy and safety of the two strategies in terms of episodes of metabolic disorders, arrhythmia, pulmonary edema, hypotension, hemorrhage and RRT dependence at hospital discharge.

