#### Sample size calculation

It has been shown that the mortality of septic shock patients who develop AKI is around 50%. Assuming an absolute reduction in mortality of 10% (55% mortality at 90 days in the delayed RRT group versus 45% in the early RRT group), 864 patients (432 per group) are required to ensure 80% power at a bilateral alpha risk of 0.05, assuming a rate of 5% non-evaluable cases.

The expected reduction of 10% in mortality was chosen as a clinically relevant difference by the study team. There are currently no data in the literature that could serve as a precedent for this, due to wide variations between existing studies in the types of patients included, the definitions of AKI used, and the definition of what constitutes early or late treatment. In light of the heterogeneous data available, a conservative estimate of a 10% reduction was retained as being clinically relevant.

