### Data collection

Detailed clinical procedure-related RRT parameters, and physiologic and laboratory data will be collected. Blood and urine will be collected at baseline, 12, 24, 36 and 48 hr and once daily thereafter until the study participants are discharged from ICU. Data will be collected on standardized case report forms (CRFs). All adverse events will be recorded on the CRF on specific pages reserved for this purpose. A simplified procedure will be used for foreseeable adverse events (hemodynamic instability, rhythm disturbances, electrolyte or acid-base imbalance, and bleeding events related to hemodialysis catheters or anticoagulants). Adverse events will be considered as serious if they cause death, are life-threatening, cause hospitalization (or prolongation of initial hospitalization), cause disability or cause permanent damage, a congenital anomaly or birth defect. Investigators must report any serious adverse event to the sponsor (the University Hospital of Dijon, France) promptly by email or telephone, followed by a written report within 48 hr. Completed CRFs will be returned to the CIC-EC and entered into a secured central database for independent quality control and centralized analysis.

Clinical data obtained will include demographic characteristics, comorbidities and prescribed and current drug therapy. Details of admission diagnoses, surgical status, and dates of hospital and ICU admission will be recorded. Detailed data on AKI and on septic shock will be recorded on the date of enrollment: interventions (i.e. mechanical ventilation, vasoactive drugs and fluid therapy), hemodynamics (i.e. blood pressure, heart rate and central venous pressure), nephrotoxic drugs (e.g. aminoglycosides, radiocontrast agents and hydroxy-ethyl starch), details of sepsis (i.e. site of infection and effectiveness of antimicrobial therapy) and acute physiology (i.e. components of severity of illness and SOFA score, simplified acute physiology score (SAPS II), urine output, fluid balance and secondary non-kidney organ dysfunction). During the trial, data will be collected on daily urine output, fluid balance, electrolytes, acid-base status, serum creatinine and urea, and components of the SOFA score. Data will be collected each day on whether the primary endpoint (mortality) has occurred, for evidence of any secondary endpoints and for criteria for trial discontinuation. Finally, any study protocol violations will be recorded.

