### Statistical analysis

All enrolled patients will be included in the main population analysis. The primary analysis will be by intention to treat (ITT). The characteristics of the two groups will be compared using the usual univariate tests (chi-squared or Fisher’s exact test for categorical variables, and analysis of variance or Mann–Whitney test for quantitative variables, as appropriate). The main comparison of the proportion of deaths at 90 days in both treatment groups will be performed using Fisher’s exact test, with secondary analysis by the Kaplan–Meier method, comparison using the log rank test, and Cox regression.

For the per-protocol analysis, patients will be grouped according to the time of initiation of the RRT. If RRT is initiated within 12 hr after the onset of the failure stage according to the RIFLE classification, then the patient will be included in the early RRT group. Conversely, if RRT is initiated >12 hr beyond this period, the patient will be included in the delayed RRT group. The per-protocol analysis will use the same techniques as the ITT analysis.

If the ITT and/or per-protocol analyses show a benefit of early (<12 hr) initiation of RRT, a secondary analysis will be performed using an extension of the proportional hazards model proposed by Abrahamowicz and MacKenzie [31] to estimate the non-proportional and non-log-linear effects, taking into account the exact time since initiation of RRT. This model will make it possible to trace the effect of initiation of RRT over time, thus visualizing whether early initiation results in lower risk of death after adjusting for major confounders, taking into account any non-proportional and/or non-log-linear effects. The main conclusion of the test will only cover the ITT analysis. Two interim analyses will be performed after the inclusion of, respectively, 200 and 400 patients.

Safety will be analyzed by assessing the frequency of arterial hypotension requiring the introduction or increase of noradrenaline, pulmonary edema due to overload, cardiac arrhythmias (ventricular tachycardia, ventricular fibrillation, torsade de pointes and atrio-ventricular block grade III), severe metabolic disorders and blood transfusions (≥3 units of packed red blood cells) in both groups and comparing rates using the appropriate tests, with an alpha risk set at 0.05.

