#### Secondary analyses

1. An analysis identical to the primary analysis, studying mortality at 28 days taking an alpha risk of 0.05.

2. Average length of ICU stay and in-hospital stay will be described and compared for survivors.

3. The number of days without mechanical ventilation and the number of days without RRT in the two groups will be compared. Deceased patients are considered as having a number of days without mechanical ventilation and without RRT equal to zero. The numbers of days will be compared in both groups using a Mann–Whitney test.

4. Dependence on dialysis at hospital discharge will be compared between groups using the chi-squared or Fisher’s exact test. If the groups appear imbalanced in terms of the pre-existence of non-dialyzed chronic renal failure or administration of nephrotoxic drugs, then logistic regression will be performed to adjust for these factors.

5. The frequency of occurrence of at least one episode of hypotension requiring the introduction or increase of noradrenaline, pulmonary edema due to overload, cardiac arrhythmias (ventricular tachycardia, ventricular fibrillation, torsade de pointes and atrio-ventricular block grade III), severe metabolic disorders and blood transfusions (≥3 units of packed red blood cells) will be compared between groups using the chi-squared or Fisher’s exact test.

6. The number and characteristics of patients in the delayed RRT group for whom the occurrence of a criterion for emergency RRT was observed will be described.

These comparisons will be performed by ITT and per protocol. All analyses will be performed using SAS Version 9.2 (SAS Institute Inc, Cary, NC, USA) by the team of statisticians at the CIC-EC of the University Hospital of Dijon, France. The significance level is set at 0.05 for all final analyses.

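### Hemorrhage is a named safety objective, but both fixed lists of safety comparisons reach it only indirectly, through transfusion of 3 or more units

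*Protocol article*

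**What the plan says.** **Objective.** The second group of secondary objectives in the protocol article compares the strategies on metabolic disorders, "arrhythmia, pulmonary edema, hypotension, hemorrhage and RRT dependence at hospital discharge".

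**Data.** Data collection states: "All adverse events will be recorded on the CRF on specific pages reserved for this purpose". Among the foreseeable events handled by a simplified procedure it names "bleeding events related to hemodialysis catheters or anticoagulants".

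**Analysis.** The safety comparisons are listed twice. The safety paragraph of Statistical analysis lists hypotension, pulmonary edema, arrhythmias and then "severe metabolic disorders and blood transfusions (≥3 units of packed red blood cells) in both groups and comparing rates using the appropriate tests". The significance level for these tests is 0.05. Item 5 of Secondary analyses repeats the list, again with "blood transfusions (≥3 units of packed red blood cells") as its last event, and names the chi-squared test or the exact test as the method. Neither list mentions hemorrhage or bleeding, and nothing in the article says that transfusion stands for it.

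**The concern.** Bleeding and transfusion are different outcomes. A bleed that needs fewer than 3 units does not count in the transfusion item, and a patient given 3 units for another reason does.

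The distinction matters because bleeding is tied to the procedure under test. The Renal replacement therapy section requires a large-bore catheter and permits systemic anticoagulation. Under Initiation of RRT, early-arm patients have a catheter placed at once, while delayed-arm patients who recover renal function need not be dialyzed. Exposure to catheter and anticoagulant is therefore likely to differ between arms by design. If the list is followed as written, a reader looking for the hemorrhage result would find only a treatment given at the clinician's discretion in an open-label trial.

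**Working it through.** **Step 1: objective against analysis lists.**

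| Harm in Objectives | Form in Statistical analysis and Secondary analyses |
|---|---|
| Metabolic disorders | Severe metabolic disorders |
| Arrhythmia | Four named rhythm disturbances |
| Pulmonary edema | Pulmonary edema due to overload |
| Hypotension | Hypotension needing noradrenaline to be started or increased |
| RRT dependence | Secondary analyses, item 4 |
| Hemorrhage | Not named; the remaining item is "blood transfusions (≥3 units of packed red blood cells") |

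The other harms keep their name and gain a qualifier. Hemorrhage alone has no item under its own name.

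**Step 2: data collected against analysis lists.** Of the four kinds of foreseeable event in Data collection, hemodynamic instability, rhythm disturbance and electrolyte or acid-base imbalance each have a counterpart in the lists. Bleeding does not.

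**Step 3: the arm size used below.** The only computed figure in the article is the sample size for "55% mortality at 90 days in the delayed RRT group versus 45% in the early RRT group". At two-sided 0.05 and 80% power, the two-proportion formula gives 392 per arm without continuity correction. That is 784 in total, or 826 after dividing by 0.95. With continuity correction it gives 412 per arm, 824 in total: 824/0.95 = 868 and 824 × 1.05 = 866. The stated 864 (432 per arm) reproduces with the correction. This point does not depend on that figure; 432 per arm is only carried forward.

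**Step 4: how well transfusion tracks bleeding (assumed rates).** Let p be the proportion of patients who bleed, s the share of bleeds that lead to 3 or more units, and b the proportion transfused that much for other reasons. If these are independent, the transfusion rate is q = 1 − (1 − p·s)(1 − b). Power is for two proportions, 432 per arm, two-sided 0.05.

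Direct comparison of bleeding: 10% v 15% has 60.4% power; 10% v 20% has 98.5%.

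| s | b | Transfusion rates if bleeding 10% v 15% | Power | Transfusion rates if bleeding 10% v 20% | Power |
|---|---|---|---|---|---|
| 0.3 | 0 | 3.0% v 4.5% | 21.2% | 3.0% v 6.0% | 56.6% |
| 0.3 | 0.1 | 12.7% v 14.1% | 8.4% | 12.7% v 15.4% | 20.6% |
| 0.3 | 0.2 | 22.4% v 23.6% | 6.2% | 22.4% v 24.8% | 12.9% |
| 0.5 | 0 | 5.0% v 7.5% | 32.9% | 5.0% v 10.0% | 79.8% |
| 0.5 | 0.1 | 14.5% v 16.8% | 14.7% | 14.5% v 19.0% | 42.5% |
| 0.5 | 0.2 | 24.0% v 26.0% | 10.0% | 24.0% v 28.0% | 26.8% |
| 0.8 | 0 | 8.0% v 12.0% | 50.0% | 8.0% v 16.0% | 95.3% |
| 0.8 | 0.1 | 17.2% v 20.8% | 27.0% | 17.2% v 24.4% | 74.2% |
| 0.8 | 0.2 | 26.4% v 29.6% | 18.1% | 26.4% v 32.8% | 54.0% |

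Transfusion is the weaker comparison in every row, by anything from a little (95.3% against 98.5%) to a great deal (12.9% against 98.5%).

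**Step 5: relative risk with equal background.** Take bleeding of 10% early and 5% delayed (true relative risk 2.0) and s = 0.5.
- b = 0: 5.0% v 2.5%, relative risk 2.0.
- b = 0.05: 1 − 0.95 × 0.95 = 9.75% v 1 − 0.975 × 0.95 = 7.375%, relative risk 1.32.
- b = 0.20: 1 − 0.95 × 0.80 = 24% v 1 − 0.975 × 0.80 = 22%, relative risk 1.09.

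**Step 6: unequal background.** Keep s = 0.5.
- Bleeding 10% early v 5% delayed, b = 0.1 early and 0.2 delayed: 1 − 0.95 × 0.9 = 14.5% v 22%, relative risk 0.66. The true excess is reversed.
- Bleeding 5% in both arms, b = 0.2 early and 0.1 delayed: 22% v 1 − 0.975 × 0.9 = 12.25%, relative risk 1.80. An excess appears where there is none.

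Dilution towards no difference is therefore not guaranteed. It rests on equal non-bleeding transfusion in the two arms.

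**The case against.** The analysis lists can fairly be read as operational definitions. Objectives gives short labels and the lists give each a measurable, mostly severity-limited form; on that reading, 3 or more units is simply how major hemorrhage is measured. The mapping in step 1 is one-to-one once transfusion is matched to hemorrhage, and restricting arrhythmia to four rhythms leaves nobody saying that arrhythmia goes unanswered. This stands as far as it goes: a reader might infer that the hemorrhage objective is not answered at all, and the article does not support that.

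A reader might also infer that the recorded bleeding events will never be compared. That is not shown either. This is a condensed article, and a full protocol or analysis plan may tabulate adverse events by arm. What can be faulted is that the list the article does fix, twice, departs from its own objective without saying so.

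Catheter- or anticoagulant-related bleeding would itself be an imperfect endpoint. It is narrower than hemorrhage, and its attribution rests with unblinded investigators. Both criticisms stand, so all recorded bleeding should lead. It is also said that delayed-arm patients who never receive a catheter cannot have a catheter bleed. In a comparison of strategies by randomized arm that is part of the effect, and those patients count as event-free.

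Finally, every rate in steps 4 to 6 is assumed. That stands too: the calculations show a range and do not establish that a harm would be hidden.

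**Conclusion.** The point holds in limited form. Hemorrhage is a stated objective and bleeding is recorded, yet the fixed comparisons reach it only through transfusion of 3 or more units, an undeclared and non-specific proxy. The objective is answered indirectly and incompletely.

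The size of the effect cannot be given, because the article states no bleeding or transfusion rate. Under the assumed rates with equal background transfusion, the proxy runs from slightly to much less sensitive than a direct comparison; with unequal background the bias can take either sign. A claim that the trial would conceal a bleeding harm goes beyond the documents.

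The weight is minor. One component of a secondary safety objective is affected; the primary analysis, sample size and main conclusion are not.

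**What to change.** In the safety paragraph of Statistical analysis and in item 5 of Secondary analyses, add: patients with at least one bleeding event recorded as an adverse event on the CRF, compared by randomized arm with the chi-squared or Fisher's exact test. Count all bleeding first and show catheter- or anticoagulant-related bleeding as a subset. Keep transfusion of 3 or more units as a separate item.

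The cost is one more safety test on data already collected. The weakness is that attribution of a bleed to catheter or anticoagulant depends on the investigator in an open-label trial, which is why the all-bleeding count should be the leading result.
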